### Assignment of the intervention

#### Randomisation

Randomisation will be completed by a web-based service, at the King’s Clinical Trial Unit (KCTU, [33]). Randomisation will be done on an individual level, minimising by trial site (London or Southampton) and gender of the infant (male or female). Allocation is performed when a trained, unblinded researcher logs into the KCTU system, and the system then sends an automatic email to the researcher confirming the allocation of the participant. This procedure will be performed after the baseline assessments have been completed, before the first attention training/control session.

#### Blinding

Researchers who administer the baseline and outcome assessments will be blind to treatment condition. Efforts will be made to ensure that parents are also blind to treatment condition. To maintain parent blindness throughout the trial the number of home visits, contact with trainers, and set-up procedures will be identical between the intervention and control groups. At the end of the trial, a qualitative interview will be conducted with the primary parent/caregiver to assess whether they have remained blind to treatment condition throughout the intervention period. Due to the nature of the intervention, it will not be possible for the researchers who administer the attention training to remain blind to the treatment condition. However, the treatment and control conditions are run using automated MATLAB scripts and data metrics from these tasks will be analysed by different, blinded researchers. The researchers who administer the intervention will not be involved in the collection of outcome data. The only exception to this will be the intermediate outcome assessment. Researchers who conduct the intermediate outcome assessment will not be blind to treatment condition. To note, data from the intermediate assessment is not included as any of the primary or secondary outcomes.

#### Adherence and fidelity

Adherence to the trial will be judged to exist as a minimum of six training/control sessions per infant, with a minimum average session duration of seven min. Fidelity will be measured as the percentage of eye-tracking data collected across training/control sessions (i.e. the amount of time the infant was looking towards the screen and the eye-tracker was detecting their gaze).

### Outcomes

A summary of all measures collected in the trial can be found in Additional file 1: Table S1. Data for the primary and secondary outcomes will be collected before and after the intervention period, both in the laboratory and in the home. The infant’s parent will be present for all measures collected during these assessments. Parents are asked to respond to their infant’s needs but not to actively initiate interaction with their infant or try to direct their attention. Visits to the laboratory take approximately 5 h. Parents will be reminded at the start of each session that they can ask to stop or take a break at any time for any reason. All infant assessments will be videotaped whenever feasible.

#### Primary outcome

The primary outcome in the trial will be a composite of eye-tracking measures used to assess changes in infant attention control. This eye-tracking data will be collected in the home, using a 20-min eye-tracking battery designed to measure different aspects of infant attention. The tasks included in the battery are the: cognitive control task, sustained-attention task, sequence learning task, distractor task, visual paired comparison task, and gap-overlap task (see Table 1 for a description of each task). From this battery, three eye-tracking measures were selected for the primary outcome composite, based on their responsiveness to attention training in previous replications of the intervention [24]:

**Table 1 Tab1:** Summary of eye-tracking battery

Task	Summary
*Cognitive control* adapted from [24, 49]	At the beginning of each trial, the infant is presented with a fixation point in the centre of the screen. Once the infant looks to the fixation point, an audio reward is presented, followed by a visual reward (a short animated clip), which is presented on either the left or right of the screen. The visual reward is presented on 1 side for 9 consecutive trials (pre-switch) before switching to the other side for the subsequent 9 trials (post-switch). Anticipatory saccades are coded based on the child’s looking behaviour during the anticipatory window (between the start of the auditory reward and the start of the visual reward). The dependent variable is the percentage of trials in which infants make a correct anticipatory saccade towards the location of the target stimuli in the pre- and post-switch phases.
*Sustained attention* adapted from [24]	The infant is presented with two ‘interesting’ (complex, detailed) and two ‘boring’ (noncomplex) static stimuli. For each stimulus, the experimenter records the length of the first 5 of the infant’s looks towards the stimulus presentation area. To qualify as a look the infant must visually engage with the stimulus for at least 1 s. To terminate the look, the infant must disengage from the stimulus for at least 1 s. The longest of the first 5 looks is termed the peak look duration. The dependent variable is the peak look duration towards the interesting stimuli.
*Gap-overlap* adapted from [47, 50]	The infant is presented with a stimulus in the centre of the screen. Once the infant fixates on this central stimulus, a peripheral stimulus appears on the left or right of the screen. When the infant moves their gaze from the central to the peripheral stimulus they receive an audiovisual reward. There are three conditions in this task: baseline, overlap and gap. In the baseline condition, the central stimulus disappears at the same time that the peripheral stimulus appears. In the gap condition, there is a 200-ms gap between the removal of the central stimulus and the appearance of the peripheral stimulus. In the overlap condition, the central stimulus remains on the screen after the peripheral stimulus appears. The dependent variable is the saccadic reaction time (ms) to move the eyes from the central to the peripheral stimulus in the overlap condition.
*Sequence learning* adapted from [51]	The infant is presented with a target cartoon character (e.g. a bunny rabbit) that can appear in one of 6 locations. If the infant moves their gaze to the correct target location prior to the emergence of the cartoon character then they receive an audiovisual reward. For the first 8 trials, the character appears in a sequence of locations 1, 3, 5. After 8 trials the sequence reverses. The dependent variable is the proportion of correct anticipatory saccades towards the target location.
*Visual paired comparison* adapted from [52]	The infant is presented with a static image (Image A) in the centre of the screen. Image A is presented until the infant has looked at it for a total of 10 s. Following this 10-s period, Image A is presented alongside a new image, Image B. The dependent variable is the infant’s look duration towards the new versus the familiar stimulus.
*Distractor* adapted from [53]	An animated cartoon is presented in the centre of the screen. Throughout its presentation, distractors randomly appear on the left or right side of the screen. If the infant looks towards the distractors then the cartoon is paused. The dependent variable is the number of looks towards the distractors.

Sustained attention (an infant’s ability to maintain their attention on a stimulus). This will be measured as the peak duration of infant looking time towards a series of interesting static stimuli in the sustained-attention task. Peak look duration is defined as the longest of the first five individual looks towards each stimulusDisengagement effect (an infant’s ability to disengage their attention from a stimulus). This will be measured as the difference between mean saccadic reaction times between the baseline and overlap conditions in the gap-overlap taskCognitive control (an infant’s ability to learn a rule, and later inhibit this information to shift attention to a new rule). This will be measured as the percentage of trials in which infants correctly anticipate the location of the target stimuli in the pre- and post-switch phases of the cognitive control task.

#### Secondary outcomes

Secondary outcomes were selected to assess whether changes in infant attention control following attention training transfer to more naturalistic contexts. The following measures will be secondary outcomes in the trial:Parent-report measures of infant executive attention assessed by the Infant Behavior Questionnaire-Revised [34], including the effortful control, activity level and duration of orienting scalesObservational measures of infant attention to toys during toy play including the task orientation episode from the Laboratory Temperament Assessment Battery, Lab-TAB [35], and a structured free-play episode adapted from [36]. Behavioural coding will be completed using an in-house coding scheme and the Lab-TAB manualObservational measures of infant social attention skills using the Early Social Communication Scales (ESCS) [37]. The following ESCS tasks will be administered: responding to the joint attention task, the social interaction task, the initiating joint attention task, and the book-reading task. Infant behaviours will be coded according to the ESCS manualGeneral attentiveness as measured by infant average look duration to the stimulus presentation area across the entire 20-min eye-tracking battery

#### ADHD symptom trajectories

Follow-up visits to the laboratory will be completed at 2 and 3 years of age. At age 3, standardised measures will be used to assess the presence of early ADHD symptoms including the Child Behaviour Checklist [38], the young child Diagnostic Interview Schedule for Children [39], and the teacher and parent-report Conners’ Early Childhood [40], as well as measures of executive function (the Behavioural Rating Inventory of Executive Functions [41]).

### Data collection and management

#### Sample size and power

Wass et al. [24] found an effect size of 0.69 on the cognitive control task following the attention training intervention in a sample of typically developing infants. Based on this effect, a sample of 50 participants (25 in each condition) is required to allow for sufficient power. This sample size will allow for 10% attrition (*n1* = 22, *n2* = 23), with 82% power and a two-tailed significance value of 0.05, using an analysis of covariance (ANCOVA) with baseline-outcome correlation of 0.6 (Stata 14 *sampsi,*) [42].

#### Data management

Parent-report measures will be stored using a secure online database called REDCap (Research Electronic Data Capture) [43]. To ensure blinding, only unblinded researchers will have access to the INTERSTAARS REDCap database. A subset of data (10%) will be double entered into REDCap to assess reliability of data entry across researchers. Experimental data (e.g. eye-tracking and neurophysiological measures) will be stored on a secure server at the CBCD.

#### Statistical methods

An intention-to-treat (ITT) approach will be used to analyse data from the trial, which will follow a Statistical Analysis Plan specified prior to data inspection, approved by the Data Monitoring and Ethics Committee, with analyses undertaken with uninformative treatment group labels. The primary outcome measure will be a composite of the three eye-tracking components selected above in ‘Outcomes’. The three components will be analysed together initially for evidence of a common treatment effect, equivalent to a treatment effect for the simple sum of normalized standardized scores of each component. A multivariate ANCOVA will then be used to test the treatment effect of the attention training group compared to the control group, using Stata *sem* [42].

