#### Missing data

Missing baseline and outcome data will be treated as ignorable under the assumption of missing-at-random. This assumption can be made due to the repeated measures set-up in which both baseline and outcome variables are treated as dependent variables with all valid scores for each component included.

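### Unless the SAP adds a small-sample correction, the primary multivariate ANCOVA in Stata sem on about 45 infants runs at roughly 6–12%, not the stated two-sided 5%

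*Protocol article*

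**What the plan says.** Under Statistical methods, the three eye-tracking components are first analysed together for a common treatment effect, described as "equivalent to a treatment effect for the simple sum of normalized standardized scores of each component". The second step in that section is a multivariate ANCOVA, of which the article writes that it "will then be used to test the treatment effect of the attention training group compared to the control group, using Stata"; the command named is sem. The same section defers to a Statistical Analysis Plan, which is not shown.

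Under Missing data, ignorable missingness is justified by a set-up in which "both baseline and outcome variables are treated as dependent variables with all valid scores for each component included".

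Under Sample size and power, "a sample of 50 participants (25 in each condition) is required"; after 10% attrition the arms hold 22 and 23. The calculation is made "with 82% power and a two-tailed significance value of 0.05", with a "baseline-outcome correlation of 0.6" and an effect of 0.69 taken from one component, the cognitive control task.

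The article does not name the estimator, the test statistic (Wald or likelihood ratio), the reference distribution, the covariates or any finite-sample adjustment.

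**The concern.** Naming sem, treating baselines as responses and keeping all valid scores under missing-at-random together point to full-information maximum likelihood. In that framework the residual variances are divided by n rather than by the residual degrees of freedom, and the statistic is referred to z or chi-square rather than t or F. With hundreds of participants neither matters. With 45, the first makes standard errors too small, the second makes the critical value too low, and the two add up.

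At stake is the type I error of the single primary analysis. The sample-size section promises 5%, and the stated method would not deliver it without a correction. The confidence interval around the treatment effect would be too short for the same reason.

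**Working it through.** **Inputs from the article.** n1 = 22, n2 = 23 (n = 45); effect 0.69 SD; baseline-outcome correlation 0.6; two-sided alpha 0.05; three components.

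**Inputs assumed.** Multivariate normal data, no missing scores, and k mean parameters per outcome equation: k = 2 (intercept, treatment), 3 (plus one baseline), 5 (plus all three baselines), 7 (plus site and sex). With complete data, modelling three baselines jointly with the outcomes, with unrestricted covariance and no treatment effect on the baselines, gives the same effect estimate as adjusting for all three. That makes k = 5 the case closest to the article's description.

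**Step 1: the plan's own figure.** Residual SD = sqrt(1 − 0.6²) = 0.8. SE = 0.8 × sqrt(1/22 + 1/23) = 0.2386. 0.69/0.2386 = 2.892. Power = Φ(2.892 − 1.960) = 82.4%. The stated 82% reproduces. A t reference with 42 df gives 80.7%.

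**Step 2: exact size of the uncorrected tests.** Let ν = n − k.

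- 1-df Wald on the simple sum: 2P(t_ν > 1.960 × sqrt(ν/n)). For k = 3: 2P(t_42 > 1.894) = 6.5%.
- 1-df likelihood ratio: 2P(t_ν > sqrt(ν(exp(3.841/n) − 1))).
- 3-df Wald: P(F(3, ν − 2) > 7.815(ν − 2)/(3n)). For k = 5: P(F(3, 38) > 2.200) = 10.4%.
- 3-df likelihood ratio: P(F(3, ν − 2) > (exp(7.815/n) − 1)(ν − 2)/3). For k = 5: P(F(3, 38) > 2.402) = 8.3%.

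| k | Sum, Wald | Sum, LR | 3-df Wald | 3-df LR |
|---|---|---|---|---|
| 2 | 6.2% | 5.7% | 8.4% | 6.6% |
| 3 | 6.5% | 6.0% | 9.0% | 7.1% |
| 5 | 7.2% | 6.6% | 10.4% | 8.3% |
| 7 | 8.0% | 7.4% | 12.0% | 9.6% |

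**Step 3: common effect constrained equal across components.** This was simulated with 20,000 runs per setting, observed-information standard errors, and correlation between components of 0 or 0.3 (assumed). Wald: 8.2–8.4% at k = 5 and 8.9–9.0% at k = 7. Likelihood ratio: 7.6–7.8% and 8.2–8.3%.

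**Step 4: comparator.** OLS ANCOVA of the sum on its baseline sum with a t reference has size 5% under these assumptions. Simulations gave 4.6–5.6%.

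**Step 5: interval width.** For the simple sum, the ratio of ML to t half-width is 1.960 × sqrt(ν/n)/t_ν. For k = 2: 1.916/2.017 = 0.95. For k = 5: 1.848/2.021 = 0.91. For k = 7: 1.801/2.024 = 0.89. The interval is 5–11% too narrow.

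**Step 6: missing scores, direction only.** A rough simulation of the joint model (2,000 runs for each missing-data setting) gave a 3-df Wald size of 13.7% with 10% of scores missing and 19.4% with 20%. The simple sum gave 8.8% and 9.0%. It used expected-information standard errors, which already gave 12.3% for the 3-df test with complete data, so only the upward trend should be read from it.

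**The case against.** The strongest reply is that the article never says maximum likelihood, Wald, z or chi-square. It is a condensed account that defers to an SAP, and test statistics, degrees of freedom and small-sample corrections usually sit there. That stands in part. The absence of a correction from the article is not itself an error, and the SAP may contain one. The point therefore rests on what the article does state, sem with all valid scores at a stated n of 45, and is conditional on the SAP.

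A reader might go further and infer a flat false-positive rate of 8–12%, or a doubling of the stated level. The documents do not support that. It fits only the 3-df Wald test, and its lower end the constrained common-effect Wald test. The simple sum, which the article calls equivalent to its common-effect analysis, gives 6–8%. The top of each range needs site and sex in the model; the article names them as minimisation factors but not as covariates.

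Nor does this undermine the sample-size calculation, which reproduces. The trial is also phase 2, and its Discussion already rules out inferring reduced ADHD recurrence and calls for larger studies, which limits the harm of a false positive.

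Finally, OLS ANCOVA on a complete composite would drop infants with a missing component, against the stated intention. That is a fair objection to that remedy used alone.

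**Conclusion.** The concern holds in conditional form. If the SAP adds no small-sample correction, the nominal two-sided 5% primary test rejects a true null about 6–12% of the time with complete data. By test: 8.4–12.0% for the 3-df Wald, 6.6–9.6% for the 3-df likelihood ratio, 8.2–9.0% for the constrained common-effect Wald and 6.2–8.0% for the simple-sum Wald. Every uncorrected variant examined exceeds 5%. Missing scores would probably push the rate up, by an amount not established here.

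The figures assume normal data, 45 analysed infants and likelihood estimation, which is inferred from the article rather than stated in it. This is a should-fix with moderate confidence: the direction is certain under uncorrected inference, but the size depends on choices that the article leaves open.

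**What to change.** Take the confirmatory p-value and confidence interval from a method that is valid at this sample size, and fix the choice in the SAP before the data are inspected. Options:

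- a mixed model for the components, baselines included as responses, with Kenward-Roger degrees of freedom; this keeps partially observed infants, as the Missing data section intends;
- OLS ANCOVA of the composite on its baseline with a t reference, where components are complete;
- a re-randomisation test that repeats the minimisation by site and sex.

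Keep the sem model as a supporting analysis. If the SAP already specifies a correction, one sentence saying so closes the point.

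The cost is wording in the SAP, slightly wider intervals and slightly lower apparent power. On the plan's own inputs, moving from a normal to a t reference takes power from 82.4% to 80.7%. No change to design or sample size follows from this point.

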#### Missing data

Missing baseline and outcome data will be treated as ignorable under the assumption of missing-at-random. This assumption can be made due to the repeated measures set-up in which both baseline and outcome variables are treated as dependent variables with all valid scores for each component included.

#### Sensitivity analysis

If more than 10% of participants are missing components of the primary outcome then a sensitivity analysis will be performed. This analysis will be completed using Stata *mi*.

### Ethical issues

#### Ethical approval

Ethical approval has been granted for the trial from the National Health Service Integrated Research Application Service, London Central Research Ethics Committee (Reference: 15/LO/0407).

#### Data monitoring

The Data Monitoring and Ethics Committee will meet biannually to discuss the INTERSTAARS trial. To monitor for possible adverse side effects of participating in INTERSTAARS, the following information will be collected regularly throughout the trial:Infant sleep: we will use a Sleep Diary (developed by our own laboratory) to measure infant sleeping patterns. Data collected includes the amount of sleep during the day and during the night, and the number of times the infant wakes during the night. The Sleep Diary will be completed for the night before, and the night following, each attention training or control sessionInfant fussiness: we will use a Fussiness Scale (developed by our own laboratory) to measure infant fussiness. Fussiness will be rated on a 1 to 5 scale for the 4 h following each attention training or control session, and for the 4 h that is comparable from the previous day, i.e. if a training session finishes at 2 p.m., fussiness will be rated from 2 p.m. to 6 p.m. for that day, and from 2 p.m. to 6 p.m. for the previous day.The Standard Protocol Items: Recommendations for Interventional Trials (SPIRIT) checklist [44] for this manuscript is included as Additional file 2.

## Discussion

INTERSTAARS is a two-site randomised controlled trial investigating the potential efficacy of nine weekly attention training sessions to improve attention control in infants at familial risk of ADHD. The trial is novel; cognitive training has not previously been applied to infants at increased risk of developing attention problems. While early psychological interventions have been championed as a way of reducing the risk for ADHD, studies have so far focussed on young children already displaying ADHD symptoms. Through its implementation in infancy, before symptoms have emerged, INTERSTAARS offers a potential preventative approach for infants at heightened risk. The intervention is home-based, making it a viable option for at-risk families. Results from the INTERSTAARS trial will make a novel contribution to research on early interventions for ADHD, and will help to further our understanding of infant attention in general.

While the trial will greatly contribute to these fields of research, potential limitations of the study should also be recognised. One difficulty encountered in the design of the trial was selecting an appropriate control condition. There were several options for control participants including: (1) treatment as usual, (2) a yoked control design and (3) a passive viewing condition. Treatment as usual was not selected because we wanted to ensure that differences between the control condition and the treatment condition were specific to attention training, and were not the result of another aspect of home visits, such as frequent interaction with researchers, or the amount of screen time. Furthermore, as INTERSTAARS targets an at-risk cohort (rather than a population already diagnosed, or exhibiting, ADHD symptoms) it is unlikely that the infants involved in the trial would have been previously receiving any form of intervention for ADHD prior to entering the trial.

In the second option for the control condition, a yoked control design, participants would view the attention training games, but the games would not be gaze-contingent. This condition appeared optimal in minimising the differences between the two conditions. However, pilot studies by SW showed that infants became bored quickly when watching the yoked control condition, making it difficult to match the conditions on overall screen time, so this condition was also not selected. Instead, a passive viewing condition was used. This is the same control condition used in previous studies with this attention training intervention [24, 28]. It allows for the conditions to be matched on screen time. However, the surface audiovisual features of what the infants view on the screen will differ between conditions.

There are also some limitations associated with using a familial risk group as the sample for the trial. Using a prospective design allows researchers to target a group of individuals who are at an increased risk of developing the disorder of interest, and to study this group in depth as they develop through infancy and beyond [45, 46]. Fifty infants at familial risk of ADHD will be recruited to the trial, a sample size that is modest enough to assess group differences following attention control training. However, it should be noted that not all of the infants included in the trial would develop ADHD without intervention. To generalise any findings to infer that attention control training leads to reduced ADHD recurrence will not be possible within this early stage trial. If significant group effects are found for attention control training in the INTERSTAARS sample then it will be important to test this approach with larger groups of infants in the future.

In addition to using larger samples, future research should also investigate the potential efficacy of attention training with other risk groups. ADHD is a heterogeneous disorder, in that different subgroups of the population may enter the disorder via different developmental pathways [47]. While the results of the INTERSTAARS trial will be relevant for infants at increased familial risk of ADHD, whether the results are also applicable to other groups of infants at risk of ADHD, e.g. premature infants [45], will require further investigation. If successful across ADHD risk groups, future research could investigate the impact of attention training on generic attention control skills, for individuals in the general population with subclinical markers of low attention control during infancy or for other developmental disorders that exhibit impaired attention control. This would be applicable to numerous other risk groups, including infants at risk of autism spectrum disorder [48]. The home-based nature of the intervention allows for it to be feasibly administered to high-risk populations who might otherwise be difficult to reach.

